# 4.2.2 Primary outcome

In this study, at least once nausea, retching or vomiting after operation, or any combination of the above symptoms within 24 h after surgery is taken as the diagnostic criteria of PONV, thereby setting PONV incidence 24h as a primary outcome.

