# 4.3 Description of research methodology

# 4.3.1 Recruitment

The study will take the First Affiliated Hospital of Xi’an Jiaotong University as the principle research center, allying with 11 Sub-Centers, Affiliated Hospital of Shaanxi University of Chinese Medicine, First Affiliated Hospital of Henan University of Chinese Medicine, First Affiliated Hospital of Henan University of Science and Technology, First Hospital of Hunan University of Chinese Medicine, General Hospital of Ningxia Medical University, Henan Provincial People's Hospital, Hunan Provincial People's Hospital, Second Hospital of Shanxi Medical University, Shanxi Provincial Hospital of Traditional Chinese Medicine, Shuguang Hospital Affiliated to Shanghai University of Traditional Chinese Medicine, Tianjin Third Central Hospital. The study will recruit the patients scheduled for laparoscopic non-gastrointestinal surgery under general anesthesia in 12 hospitals above between September 2019 and February 2021.

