### 4.3.3 Pharmacologic and non-pharmacologic intervention

Attending anesthesiologists administrated PONV prophylaxis in operation room. Dexamethasone 5 mg IV and the second-generation 5-hydroxytryptamine 3 (5-HT3) receptor antagonists palonosetron 0.075 mg are administrated before anesthesia induction as the first choice. When palonosetron was not available at some hospitals, patients received dexamethasone 5 mg (before induction) combined with tropisetron 2 mg (at the end of surgery) instead. According to the criteria of WHO acupuncture points, Neiguan (P6) and Zusanli (ST36) will be selected in this study. As shown in the Supplementary Figure 1, these acupoints are far from the operation site. P6 is located at 2 inches above palm wrist transverse striation, between the palm long tendon and the temporal flexor tendon. ST36 is located at 3 inches below EX-LE5 (the lateral pit of the patella and patellar ligament), and one transverse finger outward lateral tibia. The electrode slice has a single conductive emboss and two connecting wires, thereby enabling non-invasive, accurate and convenient stimulation. The TEAS treatments will be scheduled to conduct twice in total, respectively during anesthesia recovery in PACU (to be awake and calm, RASS = 0) and in the next-morning of surgical ward for 30 minutes.

**TEAS group:** When patients recover from anesthesia status to a degree of the Steward recovery score ≥ 4 in PACU and the endotracheal tubes are withdrawn, the first TEAS treatment will be performed. The bilateral P6 and ST36 will be pressed to achieve a tingling sensation called “de qi”, and electrode slices will be stuck and fixed on those acupoints. Interveners will connect electrode slices to electrical stimulator and select the distant-dense wave with the frequency of 2/10Hz. After adjusting the intensity to the patient’s maximum tolerance, he/she will be treated for 30 minutes. Another TEAS treatment will be performed between 9 am and 12 am in the ward on the first postoperative day; meanwhile, patients will receive routine health education including illness, diet, exercise and psychological considerations.

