## 4.4 Description of measures taken to reduce and avoid bias

### 4.4.1 Randomization

Crabyter scientific research system (Xinyu Information Technology Co., Ltd) will be used for block randomization, with four patients comprising each block. Each center will compete into block to enroll subjects. A block group will be randomly allocated into TEAS group or Sham group at a ratio of 1: 1, with four patients regarded as one block. This random method ensures that the number of patients in two groups will be essentially equal with highly efficient enrollment.

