### 5. PATIENTS SELECTION AND EXCLUSION

### 5.1 Inclusion criteria

These criteria include the following: 1) selective laparoscopic non-gastrointestinal surgery under general anesthesia; 2) age 18–50 years old, BMI 15–40 kg/m2, ASA class I–III; 3) PONV risk prediction score Apfel ≥ 3 points; 4) ability to understand, sign informed consent and coordinate intervention and evaluation.

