### 9. STATISTICAL ANALYSIS

**Sample size estimation and data analysis：**In previous studies, the PONV incidence was reported to be approximately 40%, and the PONV incidence was reduced by 7% with the TEAS treatment(19). With a significance set at 0.05, power set at 80%, the sample size required to detect differences was 742 patients in each group calculated with the Pass 11 software (NCSS, LLC. Kaysville, Utah, USA). Taking into account a loss-to-follow-up rate of about 10%, 1634 patients in total were enrolled to meet the minimum sample size requirement.

**Sample distribution:** Describes the size and loss rate of each data set, and provides detailed reasons for loss.

**Data comparability:** Preoperative baseline information, surgical information, anesthetic and antiemetic drug usage are compared between the two groups.

**Validity analysis:** The primary and secondary outcomes of the two groups are compared.

**Safety analysis:** Chi-square statistical tests are performed for the number and incidence of adverse events.

According to the intentionality analysis ITT principle, all subjects are included even if they have undergone in part of the trial process. At the same time, the efficacy and safety indicators will be included into the PP data set conformed to the schemed set, and then statistically analyzed in strict accordance with the scheme. Continuous variables will be described by means (SDs) and median (IQR), the differences between the two groups will be compared using the independent-sample T test. Categorical variables will be described by numbers (percentages), and chi-square test and Fisher's accuracy test will be used to test the incidence. Nonparametric rank sum test will be used for the grade data. *P value*<.05 will be considered statistically significant. All statistical analyses will be performed using SPSS software (version 25.0, IBM Corporation).

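### The primary test is fixed as an unadjusted chi-square although centre and Apfel score are known before randomisation: valid, but it gives up some efficiency

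*Protocol*

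**What the plan says.** Section 4.2.2 defines the endpoint as binary, "thereby setting PONV incidence 24h as a primary outcome". Section 9 (validity analysis) states only that "The primary and secondary outcomes of the two groups are compared", and its closing paragraph gives the method: "Categorical variables will be described by numbers (percentages), and chi-square test", together with Fisher's test, applied to the incidence. No section of the protocol names a stratified or covariate-adjusted analysis.

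The factors at issue are described elsewhere:

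- **Centre.** Section 4.3.1 recruits patients "under general anesthesia in 12 hospitals above between September 2019 and February 2021". On allocation, section 4.4.1 says "Each center will compete into block to enroll subjects", in blocks of four. No stratification by centre is stated there, in section 4.1, or under Prescreening and rescreening.
- **Apfel score.** Section 5.1 requires "PONV risk prediction score Apfel ≥ 3 points". The scale has four predictors (section 2), so eligible patients score 3 or 4.
- **Prophylaxis regimen.** Section 4.3.3 makes the regimen depend on the hospital: "When palonosetron was not available at some hospitals, patients received dexamethasone 5 mg (before induction) combined with tropisetron 2 mg". Section 6 gives the two regimens as plain alternatives, without that condition.

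Section 9 (data comparability) uses such information only descriptively: "Preoperative baseline information, surgical information, anesthetic and antiemetic drug usage are compared between the two groups".

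**The concern.** Eligibility is assessed the day before surgery. Randomisation takes place in the recovery unit after extubation (Prescreening and rescreening; Table 1). Centre and Apfel score are therefore true baseline variables, and adjusting for them cannot introduce post-randomisation bias. Section 2 presents the Apfel score as built from independent predictors of PONV, and the hospital-dependent regimen gives a reason to expect some variation between centres.

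Because allocation is not described as balanced within centre, the arms can differ by chance within a hospital or within an Apfel level. A crude test treats the resulting variation as noise. A stratified test removes it. At stake is some power, in a trial planned at only 80% for a 7-point difference, and some protection of the estimate against chance imbalance.

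**Working it through.** **1. The plan's own figure.** Inputs from section 9: 40% versus 33% (a 7-point reduction), alpha 0.05, power 80%. Sidedness is not stated; two-sided is assumed here. The plain two-proportion formula is

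n = [z(0.975)·√(2·p̄·(1−p̄)) + z(0.80)·√(p1(1−p1) + p2(1−p2))]² / (p1−p2)², with p̄ = 0.365.

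- First term: 1.960 × √0.46355 = 1.3344
- Second term: 0.8416 × √0.4611 = 0.5715
- n = (1.9059)² / 0.0049 = 741.3, rounded up to 742 per group

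This matches the protocol, so the design rests on the unadjusted test.

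**2. Crude versus stratified test.** The gain depends on how prognostic the factors are. The protocol does not say, so a range was simulated. Each setting used 4,000 trials of 1,484 patients (2 × 742), 12 centres of unequal size, and blocks of four not stratified by centre. Marginal rates were set to 40% versus 33%. Assumed inputs: a normal centre effect on the log-odds scale, 35% of patients with Apfel 4, and 4 of the 12 centres on the alternative regimen. Regimen is constant within centre, so stratifying by centre absorbs it.

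The stratified test is Cochran-Mantel-Haenszel over centre × Apfel (up to 24 strata):

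z = Σ(x_k − n1_k·m_k/n_k) / √Σ[n1_k·n0_k·m_k·(n_k−m_k) / (n_k²(n_k−1))],

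where, in stratum k, x_k is the number of events on TEAS, m_k all events, n1_k and n0_k the arm sizes, and n_k the total.

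| Assumed effects (centre SD; Apfel OR; regimen OR) | Crude power | Stratified power | Change (points) |
|---|---|---|---|
| None (0; 1; 1) | 80.4% | 79.4% | −1.0 |
| Mild (0.3; 1.5; 1.3) | 80.6% | 80.9% | +0.3 |
| Moderate (0.5; 2.0; 1.5) | 80.9% | 83.4% | +2.5 |
| Strong (0.8; 2.0; 1.5) | 81.2% | 85.2% | about +4 |
| Very strong (1.0; 2.5; 2.0) | 81.2% | 87.6% | about +6 |

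Under no treatment effect the crude test rejected in 4.8% to 5.2% of trials and the stratified test in 4.5% to 5.1%. The Monte Carlo standard error of one power figure is √(0.8 × 0.2 / 4000) = 0.6 points. Both tests were run on the same simulated trials, so their difference is more precise than two separate figures would be.

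A separate set of runs at 1,484 patients, crude versus stratified, gave 79.3/79.0% (no effect), 80.4/81.1% (mild), 78.5/80.9% (moderate) and 80.0/84.6% (strong): changes of −0.3, +0.7, +2.4 and +4.6 points.

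**3. The gain in patients.** The equivalent sample-size ratio is [(1.960 + z(stratified power)) / (1.960 + z(crude power))]².

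- Moderate: (2.930 / 2.835)² = 1.07, or about 100 of 1,484 patients
- Strong: (3.006 / 2.843)² = 1.12, or about 175 of 1,484 patients

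For scale, the whole allowance for loss to follow-up is 1,634 − 1,484 = 150.

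**4. Size of a chance imbalance.** Assume 40% of patients have Apfel 4 and a 20-point risk gap between scores 3 and 4. The standard error of the between-arm difference in that share is √(2 × 0.4 × 0.6 / 742) = 2.5 points. This moves the estimated treatment difference by about 0.025 × 20 = 0.5 point. The standard error of the treatment difference itself is √(0.4611 / 742) = 2.5 points.

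**The case against.** The strongest defence is that nothing here is wrong. An unadjusted test of a binary outcome in about 1,500 patients is legitimate, it fits an allocation scheme with no stated strata, and it is the test on which the sample size was computed. This stands: the matter is efficiency, not validity. Step 4 also shows that a typical imbalance in Apfel score is small against the standard error, and the crude standard error already allows for it.

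Second, the gain rests on inputs that the documents do not supply. With no or mild effects it is nil or slightly negative. This also stands, and is why only a range is given.

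Third, a separate SAP may exist and could add adjustment. But the protocol does more than leave the analysis open: it names the test for incidence. If the SAP already stratifies, section 9 only needs to be brought into line.

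Several stronger readings are tempting and are not supported:

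- **An Apfel odds ratio of 2.4.** A reader might take the 61%–79% in section 2 as the risks at scores 3 and 4. Section 2 gives one range for high-risk patients as a group and a lower figure, 20%, under two or three antiemetics. Every patient here receives two. Any Apfel odds ratio is therefore an assumption.
- **Differing case mix.** The protocol does not say that the hospitals differ in case mix.
- **Decisions based on baseline p-values.** Section 9 says that baseline data are compared. It states no rule that acts on the result.
- **Regimen as a third, independent source of gain.** Where regimen follows hospital, it is aliased with centre and adds nothing once centre is in the analysis.

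**Conclusion.** The point holds as one of efficiency. Section 9 fixes a crude test for the primary outcome while two baseline factors, centre and Apfel score, are available for stratification before randomisation. Stratifying by both would change power by about −1 to +1 point with no or mild covariate effects, +2 to +3 points with moderate effects, and +4 to +6 points with strong ones. These figures assume 742 evaluable patients per arm, rates of 40% versus 33%, and the centre spread, Apfel share and odds ratios listed above, none of which the documents give.

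A reader might infer that the planned test is biased or has an inflated type I error because hospitals use different antiemetics. The documents do not support that. Patients are randomised individually 1:1 after the prophylaxis has been given, and the crude test kept its 5% level in every setting simulated. The case for change is that the possible gain is several times the possible loss and costs almost nothing.

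**What to change.** In section 9:

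1. Make the primary test of 24-hour PONV incidence a Cochran-Mantel-Haenszel test stratified by centre and Apfel score (3 versus 4). Use the score recorded at screening: one of its components is postoperative opioid use, and a later re-scoring would no longer be a baseline value.
2. Fix a pooling rule for very small centres before unblinding. With 1,484 patients in 12 centres the average is about 124 per centre, so pooling matters only if recruitment is very uneven.
3. Report a risk difference with 95% CI adjusted for the same two factors (Mantel-Haenszel or standardised), so that test and interval share one adjustment set.
4. Keep the crude chi-square as a sensitivity analysis.
5. Do not give regimen its own term where it follows hospital. If it turns out to vary within hospitals, as the wording of section 6 would allow, add it in a sensitivity model only.

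The cost is one paragraph of text. Centre and Apfel score are already established at entry, and the sample size does not change. The downsides are a power loss of at most about one point in these simulations if neither factor is prognostic, and the need to pool small centres.

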### 10. QUALITY CONTROL

**Quality control system (QC)：**In this study, two quality control levels will be established. In the first level, the internal QC inspectors who will not participate in the implementation will be selected from the department. The second level quality control will be monitored by a hospital quality control officer. The quality control manager will examine, correct, and report the violative behavior of the study protocol, and check if the data record is true, timely, accurate and complete.

### 11. REQUEST FOR THE ETHICAL COMMITTEE

The study was approved by the Ethics Committee of the First Affiliated Hospital of Xi’an Jiaotong University (approval code XJTU1AF2019LSK-084) and registered with Clinical Trials Registry (NCT04043247). According to the Declaration of Helsinki requirements of informed consent, all subjects will voluntarily sign the informed consent form.

